#### **Secondary objectives**

1. To assess the seroprevalence according to vaccination status among NH residents and staff in Belgium at month 0 and at every follow-up visit in the cohort at month 2, 4, 6, 8 and 10.
2. To assess the risk of getting a SARS-CoV-2 infection since vaccination between:
  - Residents and staff
  - Seropositive and seronegative participants at all timepoints
  - Individuals with or without previous self-reported SARS-CoV-2 infections
  - Adjusted for the updated vaccination degree of NH at all timepoints
3. To assess the proportion of confirmed COVID-19 deaths and non-COVID-19 related deaths and the time until death since vaccination (within the study timeframe) between sero-positive and -negative participants for NH residents
4. To assess the duration of SARS-CoV-2 specific antibody responses (seroreversion/no antibody response) since vaccination among NH residents and staff in Belgium.

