## **2.6 Sampling procedure**

*Stratified random sampling of nursing homes.*

A stratified random sample of 69 nursing homes from NHs in Belgium will be selected. NH-related features that will be necessary for this method of sampling will be extracted from the existing Sciensano database. The RIZIV number will be necessary to identify the selected nursing homes. The nursing homes will be equally spread over Belgium and randomly sampled within the strata defined by region and province, and in proportion to the population. Random samples from the stratified province will be taken in proportional to the number of beds. The selected NHs will be contacted for agreement to participate in this study by Ghent University.

If a NH refuses to participate, a substitute NH with a comparable profile according to the strata will be contacted. The reason of refusal will be documented to assess possible selection bias.

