### **Secondary objectives**

4. To assess the seroprevalence according to vaccination status among NH residents and staff in Belgium at month 0 and at every follow-up visit in the cohort at month 2, 4, 6, 8 and 10.

The seroprevalence among NH residents and staff in Belgium at month 0, and follow-up in the cohort at month 2 (and if relevant at month 4, 6, 8, and 10), will be reported according to the vaccination status (Number of shots: 0, 1 or 2) and for the subgroups ‘with’ and ‘without’ a history of self-reported SARS-CoV-2 infection, averaged over NHs based on a GEE analysis with exchangeable covariance structure.

5. To assess the risk of getting a SARS-CoV-2 infection since vaccination between:
  - Residents and staff
  - Seropositive and seronegative participants at all timepoints
  - Individuals with or without previous self-reported SARS-CoV-2 infections
  - Adjusted for the updated vaccination degree of NH at all timepoints

For vaccinated participants only, a survival analysis will be performed to investigate the time (in days) to a SARS-CoV-2 infection since vaccination between sero-positive and -negative

participants at all time points. A participant is considered to have an event when the participant had a positive PCR test result (or a positive antigen rapid test, or a positive CT scan, or a positive saliva test in absence of a PCR test). The survival or censoring time (in days) is registered since 14 days after being fully vaccinated (full dose regimen) until first event (or censoring moment). If the proportional hazard assumption holds, a stratified (by NH) Cox proportional hazards regression model will be used to model the hazard of SARS-CoV-2 infection between sero-positive and -negative participants at all time points (modelled by the inclusion of a time-varying seropositivity status), adjusted for type of participant, history of self-reported SARS-COV-2 infections, and a time-varying NH vaccination degree. The analysis will be performed stratified by type of participant or other variables, if the proportional hazard assumption does not hold.

6. To assess the proportion of confirmed COVID-19 deaths and non-COVID-19 related deaths since vaccination and the time until death (within the study timeframe) between sero-positive and -negative participants for NH residents

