For vaccinated NH residents only, a survival analysis will be performed to investigate the proportion of deaths within the study follow-up and the time (in days) to a confirmed COVID-19 death since 14 days after being fully vaccinated (full dose regimen). The survival or censoring time (in days) is registered since 14 days after being fully vaccinated until first event (or censoring moment). A non-COVID-19 related death will be considered as a competing risk in the analysis. If the proportional hazard assumption holds, a stratified (by NH) Cox proportional hazards regression model will be used to model the cause-specific hazards between seropositive and seronegative residents. The latter will be included as a time-varying covariate. A history of self-reported SARS-COV-2 infections, a time-varying NH vaccination degree, province, age, gender, care profile, and presence of COVID-specific comorbidities will be

considered for model adjustment.

7. To assess the duration of SARS-CoV-2 specific antibody response (seroreversion/no antibody response) since 14 days after being fully vaccinated among NH residents and staff in Belgium.

The duration of SARS-CoV-2 specific antibody responses among NH residents and staff in Belgium will be modelled by means of an interval-censored survival analysis. Seroreversion will be defined as a negative rapid test result after at least one positive rapid test result or as two succeeding negative test results (implying the participant did not seroconvert after vaccination within two to four months). The time interval to seroreversion/no response is the time interval between 14 days after the (second) vaccination date (full dose regimen) and the first test moment of a negative test result after at least one positive rapid test or of the two succeeding negative rapid test results. As a sensitivity analysis, the event will also be defined as two succeeding negative rapid test results (whether or not after at least one positive rapid test result), if the rapid test result would turn out to be unstable.

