### **Tertiary objectives**

Although this study was not designed to assess vaccine effectiveness, end points will be compared between vaccinated and non-vaccinated participants, applying propensity score methods, if sufficient non-vaccinated participants occur in the random selected sample.

8. To assess the risk of getting SARS-CoV-2 infected between vaccinated and non-vaccinated (at last visit) residents/staff.

If a sufficient number of non-vaccinated participants are available in the sample, a survival analysis will be performed to investigate the time (in days) to a SARS-CoV-2 infection

since 14 days after being fully vaccinated between vaccinated and non-vaccinated participants. A participant is considered to have an event when the participant had a reported positive PCR test result (or a positive antigen rapid test, or a positive CT scan, or a positive saliva test in absence of a PCR test) during the baseline or one of the follow-up visits. The survival or censoring time (in days) is registered since 14 days after being fully vaccinated (or since 14 days after main (second) vaccination date in corresponding NH in case of non-vaccinated participants) until first event (or censoring moment).

If the proportional hazard assumption holds, a stratified (by NH) Cox proportional hazards regression model will be used to model the hazard of SARS-CoV-2 infection between staff and residents, and between vaccinated and non-vaccinated participants, adjusting for history of self-reported SARS-COV-2 infections, and a time-varying NH vaccination degree. Propensity score methods will be applied to reduce the effects of confounding. If insufficient non-vaccinated residents would be available in the cohort, the analysis will be performed for staff only.

9. To assess the proportion of confirmed COVID-19 deaths and non-COVID-19 related deaths and the time until death (within the study timeframe) between vaccinated and non-vaccinated residents.

If sufficient non-vaccinated residents would be available, a survival analysis will be performed to investigate the time (in days) to a confirmed COVID-19 death since 14 days after vaccination (or since 14 days after main (second) vaccination date in corresponding NH in case of non-vaccinated participants). A non-COVID-19 related death will be considered as a competing risk in the analysis.

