If the proportional hazard assumption holds, a stratified (by NH) Cox proportional hazards regression model will be used to model the cause-specific hazards between vaccinated and

non-vaccinated residents, adjusting for history of self-reported SARS-COV-2 infections, and a time-varying NH vaccination degree. Propensity score methods will be applied to reduce the effects of confounding.

10. To assess the duration of SARS-CoV-2 specific antibody responses (seroreversion/no antibody response) since self-reported infection in a non-vaccinated residents/staff.

If sufficient non-vaccinated participants with self-reported infection would be available in the random selected sample, a survival analysis for interval censored data will be performed to investigate the time (in days) to a SARS-CoV-2 specific seroreversion/no antibody response since self-reported, natural SARS-CoV-2 infection. A participant is considered to have an event (seroreversion/no antibody response) during the interval between a positive and a negative rapid test result during the follow-up visits, or between the between the positive test date and the first visit date in case of a negative rapid test at the first test date. If the rapid test results would turn out to be unstable, a sensitivity analysis will be performed and an event is considered after two succeeding negative rapid test results during the follow-up study visits. The survival or censoring time will be expressed as an interval in days between the positive test date until the visit date with first event (or censoring moment). A Cox proportional hazards regression model for interval censored data will be used to model the hazard of a SARS-CoV-2 specific seroreversion/no antibody response since natural infection adjusted or stratified for staff and residents.

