## FOLLOW UP VRAGENLIJST

### Vragenlijst woonzorgcentrum

(in te vullen 2-maandelijks in de week dat de test afgenomen wordt)

1. Studiereferentienummer van het woonzorgcentrum.

*Vraag 2, 3 en 4 worden enkel toegevoegd indien bij de vorige vragenlijst neen werd geantwoord.*

2. Vond er reeds een COVID-vaccinatieronde plaats in het WZC?

2.3. 1ste ronde / 2de ronde (datum)

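### The nursing-home-stratified Cox models name home-level adjusters that carry little or no information, and home-reported vaccination coverage is not updated as the objective requires

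*Protocol*

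**What the plan says.** Item numbers are those of Protocol section 3.2.

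- **Model form.** For deaths among vaccinated residents (objective 6), "a stratified (by NH) Cox proportional hazards regression model will be used to model the cause-specific hazards between seropositive and seronegative residents". Objectives 5, 8 and 9 specify the same stratification by NH.
- **Adjusters.** Objective 5 is "adjusted for type of participant, history of self-reported SARS-COV-2 infections, and a time-varying NH vaccination degree". Objective 8 is fitted "adjusting for history of self-reported SARS-COV-2 infections, and a time-varying NH vaccination degree". Objective 9 compares vaccinated with "non-vaccinated residents, adjusting for history of self-reported SARS-COV-2 infections, and a time-varying NH vaccination degree". Objective 6 adds province, but only in a list of terms to be considered: "a time-varying NH vaccination degree, province, age, gender, care profile, and presence of COVID-specific comorbidities".
- **Province as a property of the home.** Under section 2.6, homes are "randomly sampled within the strata defined by region and province".
- **What the objective asks for.** Section 2.1, secondary objective 2, repeated as item 5 in section 3.2: "Adjusted for the updated vaccination degree of NH at all timepoints".
- **What is collected from the home.** Section 2.7.2 has the home asked about a campaign at follow-up only if none had taken place by baseline. In Appendix 6.3, the Dutch follow-up form for the home covers the campaign (question 2), residents vaccinated (question 3) and staff vaccinated (question 4), under this rule: "Vraag 2, 3 en 4 worden enkel toegevoegd indien bij de vorige vragenlijst neen werd geantwoord". The French form has the same rule.

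**The concern.** There are two separate problems.

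The first is the model. Stratification by home gives each home its own baseline hazard, so a covariate shared by everyone in a home drops out of the partial likelihood. Province is such a covariate, and so is a vaccination degree with one value per home. A degree that really changes over time differs within a risk set only because participants start their clocks on different dates. What remains of it then mainly marks who was vaccinated late.

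The second is the data. The objective promises an updated degree, but the home-level form stops asking for one. The protocol gives reasons to expect change. Its table of changes dates the start of the NH vaccination campaign to 5 January 2021 and reports 15% of sampled staff unvaccinated in the first test round. Table 1 places the first blood collection in February 2021. A home that reports a campaign at baseline, possibly after its first round only, is not asked for coverage again.

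At stake is the stated adjustment. Software would drop province, and would either drop the vaccination degree or return an unstable coefficient driven by a few late vaccinees.

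**Working it through.** The protocol gives no figure for this point, so there is none to reproduce.

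**Step 1: the algebra.** In a Cox model stratified by home, the information about the coefficient of a covariate Z, evaluated at zero, is

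I = sum over events of Var(Z among people at risk in the same home at that time).

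If Z is the same for everyone in the home, each variance is 0 and I = 0.

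- Province: homes are drawn within province (section 2.6), so each home has one province and I = 0 exactly.
- Vaccination degree recorded once per home: I = 0 exactly.
- Vaccination degree truly updated: people in one home at the same follow-up time share a value if they also share a time origin. Under section 3.2 the clock starts 14 days after the participant's own full vaccination, so only differing vaccination dates create variation. For the non-vaccinated in objectives 8 and 9 the origin is one date per home, so they do not differ among themselves.

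**Step 2: how much survives if the degree is updated.** The only input taken from the protocol is 69 homes. The rest are assumptions:

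- 40 people per home, giving 342 to 395 events
- initial coverage of 60% to 95%
- a rise of 0 to 15 percentage points over 300 days, updated every 60 days
- a within-home SD of vaccination date of 0 to 14 days
- 0% to 20% of participants vaccinated 30 to 240 days later

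The degree is scaled per 10 percentage points, and province is a two-level indicator.

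| Degree | SD of dates (days) | Late share | Information, NH strata | Information, no strata | Ratio |
|---|---|---|---|---|---|
| Recorded once | 0 | 0% | 0 | 363.5 | 0 |
| Recorded once | 7 | 10% | 0 | 405.5 | 0 |
| Updated | 0 | 0% | 0 | 369.5 | 0 |
| Updated | 7 | 0% | 0.530 | 362.1 | 0.15% |
| Updated | 14 | 0% | 1.257 | 401.5 | 0.31% |
| Updated | 7 | 10% | 4.121 | 377.8 | 1.1% |
| Updated | 7 | 20% | 5.922 | 367.2 | 1.6% |

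Province had information 0 with NH strata in every run, against about 85 to 98 without strata.

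Standard errors scale with the inverse square root of information. In the most favourable row the standard error for the degree is √(367.2 / 5.922) = √62.0 ≈ 7.9 times the unstratified one. With a 7-day spread and no late vaccinees it is √(362.1 / 0.530) ≈ 26 times.

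**Step 3: the contrasts of interest.** An individual covariate (age) kept about 96% to 97% of its information under NH strata, for example 362.2 / 377.7 = 95.9%. For serostatus, a run with 69 homes of 24 gave 25.2 with NH strata and 25.7 without, a loss of 0.5 / 25.7 ≈ 2%. Only this ratio matters, since the level depends on the simulated number of events. NH stratification costs the contrasts of interest very little.

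**Step 4: the data side by side.** Section 2.1 requires the degree to be updated at all timepoints. Section 2.7.2 and both language versions of the home follow-up form stop asking once a campaign is reported. The coverage items can repeat while the answer is no, but each home ends up with one reported value.

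**The case against.** The strongest reply is that no result of interest is harmed. Serostatus, participant type, prior infection and vaccination all vary within a home. NH strata remove every fixed difference between homes, including province and a once-recorded degree. Where participants share a vaccination date, the strata absorb a changing degree as well. That all stands. A reader might infer that the analyses will be reported as adjusted when they are not, or that their hazard ratios are biased. The documents do not support that: fixed home differences are controlled more tightly by the strata than a covariate would manage.

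A reader might also infer that all four models adjust for province. Only objective 6 names it, and only as a term to consider.

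Nor is it shown that an updated degree cannot be built at all. The individual follow-up forms in Appendix 6.3 re-ask anyone who previously answered no and record a first-dose date. A rough first-dose degree could therefore be derived from the sampled participants. The protocol does not specify one, however, and it would still be nearly constant within a risk set.

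Separate staff and resident coverage would vary within a home in objectives 5 and 8, but it would be largely tied to participant type. The text names a single NH degree, and objectives 6 and 9 concern residents only.

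Finally, the source of a derived covariate can be left to a statistical analysis plan. Here, though, the protocol itself fixes the strata, the adjusters and the skip rule, and they conflict. A later analysis plan can correct the model but cannot recover home-level coverage that was never collected.

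**Conclusion.** The point holds as a fault of specification and data collection, not as a source of bias. Province in objective 6 is not estimable, and this follows from algebra alone. The NH vaccination degree in objectives 5, 6, 8 and 9 has zero information if recorded once per home. If truly updated, it kept between 0 and 1.6% of its unstratified information in the scenarios tried. That range rests on the assumed coverage rise and spread of vaccination dates, and more late vaccination would raise it.

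The contradiction between an updated degree and a coverage question that stops rests on the documents' wording alone. It does not follow that NH stratification should be abandoned in the main model. Exchanging it for an estimable vaccination-degree term is a trade-off, and the strata serve the contrasts of interest well. The change is worth making because it is cheap and the missing coverage data could not be restored later.

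**What to change.** 1. In section 3.2, keep the NH-stratified Cox model as the main model for objectives 5, 6, 8 and 9. Remove NH vaccination degree from all four, and province from objective 6. State that NH strata account for fixed differences between homes.
2. To deliver the stated adjustment, add a supplementary Cox model stratified by province, with NH as a shared frailty or with NH-clustered robust variance, that includes the time-varying degree.
3. In Appendix 6.3 (Dutch and French) and section 2.7.2, lift the skip rule from the two home-level coverage questions so that numbers vaccinated over totals are recorded at every round.
4. If coverage is not to be repeated, redefine the covariate as fixed and amend secondary objective 2 in section 2.1 and the matching text in section 3.2. A fixed degree belongs only in the supplementary model, because it cancels under NH strata.

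**Cost.** Two repeated questions per home per round, and one additional model. The supplementary model controls unmeasured home-level confounding less tightly than the main model, so it should be read beside that model and not in place of it.

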## **2.5 Sample size**

To assess the cumulative incidence after 10 months of follow-up in residential care centers in Belgium a sample of 381 participants (residents & staff) is required to estimate a proportion of 0.5 with a half-width of 5%, using a 95% Wilson score CI. As residents/staff are clustered within care facilities, the sample size will be augmented by the design effect. Assuming, 15 participants (7 residents and 8 staff) per institution after 10 months of follow-up, and an ICC of 0.12, the design effect is  $2.68 = (1 + 0.12 \times (15 - 1))$ . The total sample size required is  $1022 = 381 \times 2.68$ . At least 69 institutions, each including 15 participants, need to be included in this study, which brings the total sample size to 1035 after 10 months follow-up. In order to obtain at least 15 participants, in 69 institutions after 10 months of follow-up, assuming a drop-out rate of 0.2 and 0.4 for staff (changes in staff, sick leave and holidays) and residents (deceased, hospitalized or transferred residents), would require 22 sero-negative participants per care facility, (10 staff, 12 residents) in all 69 institutions. Assuming a seroprevalence rate of 0.5 at the baseline moment of the study would require 44 participants per care facility, (20 staff, 24 residents) in all 69 institutions.

A final sample size calculation will be performed to check whether the sample size obtained for the second research question will be sufficient for the analysis of the first research question.

To assess the seroprevalence in residential care centers in Belgium a sample of 381 participants (residents & staff) is required to estimate a seroprevalence of 0.5 with a half-width of 5%, using a 95% Wilson score CI.

As residents/staff are clustered within care facilities, the sample size will be augmented by the design effect. Based on the previous calculation, 44 participants (24 residents and 20 staff) will be sampled per institution. Assuming an ICC of 0.12, the design effect is  $6.16 = (1 + 0.12 \times (44 - 1))$ . The total sample size required is  $2347 = 381 \times 6.16$ . At least 54 institutions, each including 44 participants, need to be included in this study, which brings the total sample size to 2376 participants.

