**Versie voor deelnemende medewerkers:**

1. Gelieve uw uniek studienummer in te vullen.
2. Neemt u nog deel aan de studie (zal deze vragenlijst vervolledigd worden) ?  
Zo neen, waarom niet?

*Door de onderzoeker in te vullen*

- a. Tussentijdse afwezigheid in de studie (ziekte, vakantie, hospitalisatie ...)
- b. Deelnemer wenst niet meer deel te nemen
- a. Vermoedelijk of bewezen COVID-19 overlijden                      datum van overlijden:
- b. Niet-COVID-19 gerelateerd overlijden                      datum van overlijden:
- c. Medewerker is niet langer werkzaam in het WZC

*Vraag 3 wordt enkel toegevoegd indien voordien neen werd geantwoord.*

3. Bent u gevaccineerd tegen COVID-19?
  - a. Ja, 1 dosis
  - b. Ja, 2 dosissen
  - c. Neen
  - d. Zo ja, welk vaccin kreeg u toegediend
    - i. Het AstraZeneca/Oxford vaccin
    - ii. Het BioNtech-Pfizer vaccin
    - iii. Het Moderna vaccin
    - iv. andere
  - e. Zo ja, datum van vaccinatie (eerste spuit).
4. Bent u in de afgelopen twee maanden getest geweest op het coronavirus (via PCR/ag-sneltest/of radiologisch via CT-scan)? Ja/Nee
5. Zo ja. Bent u in de afgelopen 2 maanden (tussen de vorige testronde en nu) positief getest?  
*Meerdere antwoordmogelijkheden*
  - Ja, via PCR-test (test waarbij men via een neuswisser een staal afneemt en u na labo-analyse het resultaat krijgt)
  - Ja, via antigeen sneltest (test waarbij men via een neuswisser een staal afneemt en men binnen het kwartier het resultaat kan aflezen)
  - Ja radiologisch, via een CT-scan
  - neen
6. Zo ja, datum van 1ste positieve PCR-test of sneltest in de afgelopen 2 maanden (bij benadering)?

7. Indien COVID-19 radiologisch bevestigd werd via een CT-scan , vermeld de datum van deze CT-scan.
8. Hebt u in de afgelopen 2 maand (tussen de vorige testronde en nu) een periode 1 of meerdere van volgende symptomen ervaren, zonder dat hier een duidelijke verklaring voor was? Duid aan wat van toepassing is (meerdere antwoordmogelijkheden).
  - Hoest
  - Kortademigheid
  - Pijn op de borst
  - Smaakverlies
  - Geurverlies
  - Verergering van chronische respiratoire aandoeningen (vb. COPD, astma, chronische hoest,...)
  - Koorts
  - Spierpijn
  - Vermoeidheid
  - Loopneus/verstopte neus
  - Keelpijn
  - Hoofdpijn
  - Verlies van eetlust
  - Diarree
  - Acute verwardheid
  - Plotse val
9. Zo ja, wanneer hebt u, bij benadering, deze symptomen ervaren? Gelieve de dag aan te geven waarop deze symptomen zijn begonnen.

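### As written, the antibody-duration analyses keep participants at risk of seroreversion after a new infection, so a renewed response can be credited to the vaccination or infection that started the clock

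*Protocol*

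**What the plan says.** Protocol section 3.2, secondary objective 7: "The duration of SARS-CoV-2 specific antibody responses among NH residents and staff in Belgium will be modelled by means of an interval-censored survival analysis". The clock starts 14 days after full vaccination. On the event, the section states: "Seroreversion will be defined as a negative rapid test result after at least one positive rapid test result". Two successive negatives also count, as non-response. The only planned variation concerns how many negatives are needed: "As a sensitivity analysis, the event will also be defined as two succeeding negative rapid test results". Neither infection during follow-up nor a further dose is mentioned, and no censoring moment is named.

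Section 3.2, tertiary objective 10, concerns antibody duration "since self-reported infection in a non-vaccinated residents/staff". Its time axis is the interval "between the positive test date until the visit date with first event (or censoring moment"), with the censoring moment left undefined. The model is adjusted or stratified only for staff and residents.

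Section 2.7.1 counts either an IgM or an IgG line as positive. In Appendix 6.3, the follow-up questionnaire for staff asks at every round: "Bent u in de afgelopen 2 maanden (tussen de vorige testronde en nu) positief getest", with the approximate date. The resident version asks the same.

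**The concern.** Both objectives ask how long the response to one index exposure lasts: the completed vaccination in objective 7, the reported infection in objective 10. A rapid test that reads only positive or negative cannot tell a persisting response from a new one. Someone infected while still positive, or after losing antibodies but before the next visit, tests positive at that visit. With no exit at infection, that person remains event-free. A vaccinee with one negative test who is then infected can likewise escape the two-negatives non-response event.

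The duration estimate then mixes persistence with re-exposure. A staff-resident comparison would partly reflect who was infected more often. Elsewhere the section does take account of infection history: it defines subgroups in objective 4 and is a named or considered covariate in objectives 5, 6, 8 and 9. Objectives 7 and 10 have no counterpart.

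**Working it through.** **Comparing the texts.** The protocol gives no figure for antibody duration, so there is none to reproduce.

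| Element | Objective 7 | Objective 10 |
|---|---|---|
| Origin | 14 days after full vaccination | Date of positive test |
| Event | First negative after a positive, or two successive negatives | First negative after a positive, or negative at the first visit |
| Censoring moment | Not mentioned | Mentioned, not defined |
| Infection after the origin | No exit, no covariate | No exit, no covariate |
| Sensitivity analysis | Two successive negatives | Two successive negatives |

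Applying these definitions literally, infection after the origin does not end a participant's time at risk in either objective.

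**Size: inputs.** The two-month visit spacing and ten-month follow-up come from section 2.4. The rest is assumed: 30% true reversion by month 10; 10% or 20% infected over ten months, at a constant rate independent of waning; a perfect test; visits at months 2, 4, 6, 8 and 10 after time zero.

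**Case A: infection keeps the participant positive to study end.** A reversion is seen only if the participant is still uninfected at the next visit:

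observed = Σ (k = 1 to 5) [S(2(k−1)) − S(2k)] × (1 − b)^(k/5)

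Here b is the ten-month infection proportion. S(t) = 0.7^(t/10) for constant waning hazard, and S(t) = 0.7^((t/10)²) for a rising hazard (Weibull shape 2).

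- Constant hazard, b = 0.20: 0.0689×0.9564 + 0.0641×0.9146 + 0.0597×0.8747 + 0.0556×0.8365 + 0.0518×0.8000 = 0.265.
- Rising hazard, b = 0.20: 0.0142×0.9564 + 0.0413×0.9146 + 0.0650×0.8747 + 0.0836×0.8365 + 0.0959×0.8000 = 0.255.
- With b = 0.10, the factors are 0.9791, 0.9587, 0.9387, 0.9192 and 0.9000. The sums are 0.283 (constant) and 0.278 (rising).

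**Case B: infection restarts the waning clock.** This was simulated with the same inputs.

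| Apparent 10-month reversion (true 30%) | 10% infected | 20% infected |
|---|---|---|
| Lasting positivity, constant hazard | 28.3% | 26.5% |
| Lasting positivity, rising hazard | 27.8% | 25.5% |
| Restarted waning, constant hazard | 29.8% | 29.5% |
| Restarted waning, rising hazard | 28.8% | 27.7% |

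**Check of the remedy.** In the same simulations, censoring at the last visit before infection returns about 30% in every scenario with independent infection. If the infection hazard triples after waning, censoring gives 27% to 30%. That is still at or above the uncensored value, but no longer exact.

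**An opposing error.** Section 4.3 gives the rapid test a sensitivity of 92.9%. If errors are independent between visits (an assumption; correlated errors shrink this), a participant who never reverts has a probability of 1 − 0.929^5 = 0.31 of at least one false negative in five follow-up tests. Adding this to the scenario with 10% infected, lasting positivity and constant hazard gives an apparent reversion of about 50% against a true 30%.

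**The case against.** The strongest reply is that this is silence, not a rule. No sentence says that participants are followed through infection, and censoring details are often left to an analysis plan, which is not shown here. It stands to this extent: following through is implied by the definitions, not stated. It does not remove the point, because section 3.2 already fixes origin, event, interval and sensitivity analysis, and what it fixes does not deliver duration since the index exposure.

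Four stronger readings are tempting, and the document does not support them.

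- **Objective 10 counts later vaccinees as persistent responders.** Its population is non-vaccinated. If status is judged at the last visit, as in neighbouring objective 8, later vaccinees are excluded. That is a different problem, selection on future status. If status is judged at entry, vaccination could be the undefined censoring moment. Only reinfection is plainly open.
- **Half the cohort will be infected.** Section 2.5 uses 0.5 "to estimate a proportion of 0.5" with a given precision. That is a planning value for a confidence interval and not an infection forecast for vaccinated or previously infected people.
- **Every later dose is recorded.** In Appendix 6.3 the dose question returns only after a previous answer of no, offers one or two doses, and asks for the first-dose date. A separate vaccination-date item is to be added once applicable. Whether this captures further doses is unclear.
- **Reported duration will be too long overall.** False negatives act in the opposite direction and could outweigh this bias.

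Two reservations about the remedy also stand. Section 1 notes that mild or asymptomatic cases often go untested, so some boosts will be missed. Infection may also depend on serostatus, which makes censoring informative.

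**Conclusion.** The point holds for infection after vaccination in objective 7 and for reinfection in objective 10. Taken alone, the mechanism lowers apparent seroreversion and lengthens apparent duration. With 30% true reversion at ten months and infection independent of waning, the apparent value is about 28% to 30% at 10% infected and about 25.5% to 29.5% at 20% infected. The lower ends need lasting positivity and a rising waning hazard; the upper ends need an infection that only restarts constant-hazard waning. Every size input except the visit schedule is assumed. Only participants infected before their first recorded negative, or between the two negatives that define non-response, are affected. No claim is made about the net direction of error. These are secondary and tertiary objectives, so the change should be made but does not affect the primary results.

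**What to change.** In section 3.2, define the censoring moment for both objectives:

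1. **Infection (7 and 10).** Censor at the last rapid test before the first reported positive PCR, antigen or CT result after time zero. Report the uncensored curve alongside, because censoring may be informative and untested infections are missed.
2. **First vaccination (10).** Judge non-vaccinated status at time zero and censor at first vaccination, so that nobody is selected on later status.
3. **Further doses (7).** Confirm whether the vaccination-date item in the follow-up questionnaire captures them. Censor at a further dose only if it does; otherwise state the limitation.

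The cost is a few sentences and, for infection, one derived date per participant from a question already asked at each round. Because that question covers the time since the last round, an approximate date is usually enough to identify the preceding rapid test. Some follow-up time is lost. Item 3 may need a data check or a questionnaire clarification.
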